### Objectives

To analyze whether the ABI and arterial stiffness measures (pulse wave velocity and cardio ankle vascular index) are associated independently with the incidence of vascular events and whether they can help to improve the predictive ability of risk equations based on traditional risk factors in intermediate-risk population.

To analyze whether the postprandial capillary glucose, glycated hemoglobin, and self-blood pressure measurement are associated independently with the incidence of vascular events and whether they can help to improve the predictive ability of risk equations based on classical risk factors in intermediate-risk population.

To analyze whether the presence of comorbidity measured by composite indices (Charlson Index, Cumulative Illness Rating score) is associated independently with the incidence of vascular events and whether they can help to improve the predictive ability of risk equations based on classical risk factors in intermediate-risk population.

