### Subjects

#### Study population

Population aged between 35 to 74 years who have an intermediate cardiovascular risk, defined as coronary risk between 5% -15% at 10 years according to the Framingham adapted risk equation (because of the low incidence of coronary heart disease in our country) [26] or vascular mortality risk between 3-5% at 10 years according to the SCORE equation [27]. Exclusion criteria: terminal illness or institutionalization at the appointment time or a personal history of atherosclerotic disease. Sample selection: There will be a random sample of population aged 35 to 74 (both included) which have an intermediate cardiovascular risk. This is a multicenter project in the context of the Instituto Carlos III Preventive and Health Promotion Research Network (RedIAPP) (RETICS RD06/0018). Sample recruitment will be carried out in Health Centers belonging to 3 groups of the 3 network regions. Candidate patients will be cited by telephone at their health centre and invited to participate by signing an informed consent.

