#### Vascular events in the follow-up

There will be a telephone follow-up to the 1.5, 5 and 10 years to verify the vital status and the existence of hospital admissions due to vascular health problems. The information of each case will be confirmed after a review of hospital discharge reports and the verification of the diagnostic criteria by a consensus of at least 2 investigators. Fatal and non fatal coronary heart disease (myocardial infarction or angina pectoris) will be considered. Cases will be classified according to symptoms, electrocardiogram, and myocardial necrosis markers. Fatal cases will be classified through the death certificate or autopsy findings. Angina pectoris only will be considered if there are changes in the ECG or a positive stress test. Stroke will be considered when neurologic deficit lasting more than 24 h attributable to a diagnosis of a focal cerebral ischemia is confirmed by an imaging test (CT or MRI). Peripheral arterial disease will be considered if there is a diagnostic made by arteriography or Doppler (ankle-brachial index below 0.9) or lower limb amputation or ulcer or gangrene attributable to an ischemic deficit.

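### Read literally, the event definitions leave out a stroke that kills within 24 h or before imaging, and other non-coronary vascular deaths; the likely loss is small and rewording is cheap

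*Protocol article*

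**What the plan says.** The only event definitions are in the protocol article, Vascular events in the follow-up.

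- **Follow-up contact.** Telephone calls at 1.5, 5 and 10 years serve "to verify the vital status and the existence of hospital admissions due to vascular health problems". Under Data collection method, the follow-up questionnaire is said to record deaths as well as vascular events.
- **Coronary disease.** "Fatal and non fatal coronary heart disease (myocardial infarction or angina pectoris) will be considered". Between the coronary classification criteria and the rule for angina stands "Fatal cases will be classified through the death certificate or autopsy findings".
- **Stroke.** "Stroke will be considered when neurologic deficit lasting more than 24 h attributable to a diagnosis of a focal cerebral ischemia", and an imaging test (CT or MRI) must confirm it. Duration, ischaemic cause and imaging are all required.
- **Peripheral arterial disease.** "Peripheral arterial disease will be considered if there is a diagnostic made by arteriography or Doppler (ankle-brachial index below 0.9"), or amputation, ulcer or gangrene from an ischaemic deficit. No fatal category is given.

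Under Study population, a participant may enter on coronary risk of 5-15% or, alternatively, on "vascular mortality risk between 3-5% at 10 years according to the SCORE equation". Under Objectives, each set of markers is tested for association with vascular events and for "whether they can help to improve the predictive ability of risk equations based on traditional risk factors in intermediate-risk population", or nearly the same words.

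**The concern.** The stroke rule fits survivors who reach a scanner. A person who dies of a stroke within 24 h fails the duration requirement, and one who dies before a scan fails the imaging requirement. Other non-coronary vascular deaths, such as a ruptured aneurysm, fit none of the three categories. Taken at its word, the section would therefore class some of the most severe vascular outcomes as non-events, while angina with ECG changes and peripheral disease diagnosed by Doppler count.

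This fits poorly with a cohort admitted in part on predicted vascular mortality and followed for 10 years to improve risk prediction. At stake are a modest number of events, consistency between adjudicators faced with an early stroke death, and the absence of a defined vascular-death outcome to set beside the mortality equation.

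**Working it through.** **1. Typical cases against the written rules**

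| Case | Counts as an event? |
|---|---|
| Fatal coronary event | Yes, named explicitly |
| Ischaemic stroke, deficit over 24 h, imaged, later fatal | Yes, under the stroke rule |
| Ischaemic stroke, fatal within 24 h | No, duration not met |
| Stroke, fatal before CT or MRI | No, imaging not met |
| Ruptured aneurysm or other non-coronary vascular death | No category |
| Cerebral haemorrhage, fatal or not | No, not focal ischaemia |

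No other section changes these answers.

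**2. The plan's own figure**

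Inputs from Sample size: two-sided alpha 0.05, power 80%, risks of 3% and 6% (relative risk 2), 336 exposed and 2352 unexposed (1:7). With a log relative risk test and binomial variance:

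n exposed = (1.960 + 0.842)² × [0.94/0.06 + 0.97/(7 × 0.03)] / (ln 2)² = 331.4, so 332, and 8 × 332 = 2656.

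This is 1.2% below the stated 2688; power at 336/2352 is 80.5%. (The same formula with pure Poisson variance gives 2801.) No stated number is shown to be wrong on this point.

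Planned events at 1.5 years: 336 × 0.06 + 2352 × 0.03 = 20.2 + 70.6 = 90.7, about 91, or 3.375% of 2688.

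**3. Planned events at 5 years, constant hazard**

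1 − (1 − 0.03375)^(5/1.5) = 10.8%, and 10.8% × 2688 is about 290.

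**4. Vascular deaths, if all 2688 entered at 3-5% over 10 years**

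- 1.5 years: 1 − 0.97^0.15 = 0.46% and 1 − 0.95^0.15 = 0.77%, giving about 12 to 21 deaths.
- 5 years: 1 − 0.97^0.5 = 1.51% and 1 − 0.95^0.5 = 2.53%, giving about 41 to 68 deaths.

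**5. Non-coronary share**

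The documents give none; 20-40% is assumed.

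- 1.5 years: 0.20 × 12.3 = 2.5 to 0.40 × 20.6 = 8.2, so about 2-8 deaths, or about 3-9% of 91.
- 5 years: 0.20 × 40.6 = 8.1 to 0.40 × 68.1 = 27.2, so about 8-27 deaths, or about 3-9% of 290.

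**6. Effect on power at 1.5 years**

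If the assumed 3% described a broader definition and the written rules removed 5% or 10% of events, 86 or 82 would remain, and power by the formula in step 2 would fall from about 80% to 78% or 76%. If the 3% already describes the written definition, the planned size is unaffected and a wider definition only adds events.

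**The case against.** Several parts of the case on the other side stand.

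- **A reader might infer that fatal events count only for coronary disease.** The text does not support that. An imaged ischaemic stroke with a deficit over 24 h that later proves fatal meets the stroke rule.
- **A reader might take the absence of haemorrhage as an error.** The three outcomes are all ischaemic or atherosclerotic, in line with the exclusion of prior atherosclerotic disease and with the Background on subclinical atherosclerosis. An ischaemic-only composite is a coherent choice with a trade-off.
- **A reader might conclude that the Cox estimates are biased.** Statistical analysis does not say how other deaths are handled, and that is commonly left to a fuller document. Even if they are censored, a Cox model still estimates a cause-specific hazard, a legitimate target for an association aim.
- **A reader might expect a weaker association for home blood pressure.** The protocol gives no haemorrhagic share and no marker-specific effect, so this would be conjecture.
- **A reader might say that the study cannot test the mortality equation.** That equation is one of two alternative entry routes, the objectives do not undertake to validate it, and deaths are recorded. The fair statement is that a vascular-death outcome is not defined.

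It can also be argued that the death-certificate sentence is general, or that a condensed article leaves fatal-event rules to the full protocol. The sentence stands inside the coronary text, however, and does not waive the duration or imaging requirements for stroke. The difficulty is a criterion that the article states, not a detail it leaves out. Review by at least two investigators does not remove it, since they verify the diagnostic criteria as written. An ischaemic endpoint also gives no reason to lose an ischaemic stroke because the patient died too soon.

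**Conclusion.** The point holds in a limited form. As written, the definitions reject a stroke fatal within 24 h or before imaging and have no place for other non-coronary vascular deaths, although the information needed to count them is already sought.

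The step 5 ranges are upper-end figures: they treat every non-coronary vascular death as lost, although some would qualify as strokes. They also rest on everyone having entered by the mortality route (the article gives no split), a constant hazard, all 2688 being followed, and the assumed 20-40% share. Setting the 5-year deaths against the 91 events planned for 1.5 years would suggest a loss of up to about 30%; the comparison at the same time point gives about 3-9%. The wording should be corrected, but the planned size and the main model are not called into question by it.

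**What to change.** In Vascular events in the follow-up:

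1. State that classification by death certificate or autopsy applies to all vascular deaths, and that these count as events.
2. State that stroke counts if the deficit lasts more than 24 h or leads to death earlier, and that imaging is not required when death precedes it.
3. Report vascular death on its own at 5 and 10 years.
4. Record haemorrhagic stroke as a separate type for a sensitivity analysis; the sponsor may keep the main composite ischaemic and should then say so.

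The cost is a change of wording, best made before adjudication. Vital status is already checked, and a death cannot be classed as coronary or not until its certificate or autopsy has been read. The small downside is that a few certificate-based deaths of less certain cause enter the composite.

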#### Sample size

The ABI < 0.9 population proportion with no history of vascular disease has been taken into account because ABI is the risk factor among those studied that we anticipate will have a lower prevalence. It is expected that in one year and a half of follow up 3% of the participants will present a vascular event. Therefore, accepting a 0.05 alpha risk and a 0.2 beta risk in a bilateral contrast, 336 subjects are needed in the exposed group and 2352 in the non-exposed group (2688 total) to detect a minimum relative risk of 2. We assumed an incidence rate in the unexposed group of 3%. Estimating a 25% of loss rate until 3360 participants will be oversampled. Poisson approximation has been used. The estimated relative risk is based on previous observational studies in which patients of the risk group had twice the incidence of vascular disease if they had an ABI < 0.9 [9]. In Catalonia node centers 1900 participants are expected to be recruited and 400 participants in each of the other two nodes. Professional nurses assigned to each health center will perform the physical examination and questionnaires. They will explain how to record the self-measurement of blood pressure and capillary blood glucose and the candidates will be cited later to collect this information. At the same time they will be scheduled for a fast blood test.

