#### Intermittent claudication

The Edinburgh validated questionnaire will be used [33]. Existence of asymptomatic PAD will be considered when ABI values are < 0.9 and no intermitent claudication are registered in the questionnaire.

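### A PAD diagnosis by Doppler ABI below 0.9 counts as a follow-up event, although ABI below 0.9 at baseline is the exposure that sizes the study; this biases the ABI result upward by an unknown amount

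*Protocol article*

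**What the plan says.** All references are to the protocol article.

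- **Objectives.** The first objective asks whether ABI and the arterial stiffness measures "are associated independently with the incidence of vascular events and whether they can help to improve the predictive ability of risk equations" built on traditional risk factors.
- **Sample size.** The calculation is built on one exposure: "The ABI < 0.9 population proportion with no history of vascular disease has been taken into account". It needs 336 exposed and 2352 unexposed participants for a relative risk of 2, with 3% incidence in the unexposed at 18 months. The effect size comes from earlier observational work in which "patients of the risk group had twice the incidence of vascular disease if they had an ABI < 0.9".
- **Intermittent claudication.** The baseline finding already carries a disease label: "Existence of asymptomatic PAD will be considered when ABI values are < 0.9 and no intermitent claudication are registered in the questionnaire".
- **Study population.** The exclusions are "terminal illness or institutionalization at the appointment time or a personal history of atherosclerotic disease". A low ABI first found at the study examination is not among them, and it could not be, since those people are the exposed group.
- **Vascular events in the follow-up.** Alongside coronary disease and stroke: "Peripheral arterial disease will be considered if there is a diagnostic made by arteriography or Doppler (ankle-brachial index below 0.9"), or amputation, ulcer or gangrene of ischaemic origin. Ascertainment is described as "There will be a telephone follow-up to the 1.5, 5 and 10 years to verify the vital status and the existence of hospital admissions" for vascular problems, followed by review of discharge reports and "verification of the diagnostic criteria by a consensus of at least 2 investigators".

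Nothing in the article separates the baseline use of the 0.9 cut-off from its use as an event criterion.

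**The concern.** Exposure and one event criterion are the same quantity at the same threshold. For that criterion, people with a low baseline ABI are prevalent cases and not people at risk of a new event. If such a person is admitted for a vascular problem and PAD is recorded, the investigators check the diagnostic criteria and find one of them satisfied. It may have been satisfied on the day of enrolment. An unexposed participant has to cross the threshold during follow-up to be counted in the same way.

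The asymmetry runs in one direction only, in favour of ABI. It enters both parts of the ABI objective: the independent association, and the gain in prediction over the traditional risk factors. The planned Cox adjustment for those factors does not remove it, because the overlap is between the exposure and the outcome and does not arise from a confounder. The planned follow-up at 5 and 10 years leaves more time for such diagnoses to accrue.

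**Working it through.** **1. The plan's own figure.** Inputs from Sample size: two-sided alpha 0.05, power 0.80, unexposed risk p0 = 0.03, relative risk 2 so p1 = 0.06, and k = 2352/336 = 7 unexposed per exposed.

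Pooled Poisson formula: n_exposed = (1.960 + 0.842)² × pbar × (1 + 1/k) / (p1 − p0)²

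- pbar = (0.06 + 7 × 0.03)/8 = 0.03375
- n_exposed = 7.849 × 0.03375 × (8/7) / 0.0009 = 336.4

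This reproduces 336 exposed, 2352 unexposed and 2688 in total. The sample-size arithmetic is not in question here; the issue lies in the event definition.

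**2. How few relabelled cases matter.** At 3% risk the exposed group yields 0.03 × 336 = 10.1 events. At the design relative risk it yields 0.06 × 336 = 20.2. The difference is about ten people.

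**3. Size of the bias under an assumed relabelling rate.** Let x be the share of exposed participants recorded as PAD events only because of the low ABI they already had. The documents give no value for x, so it is an assumption shown over a range. Assume no true effect, so that risk is otherwise 3% in both groups.

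- Observed relative risk = (0.03 + x)/0.03
- Rejection = probability that a pooled two-sided two-proportion test at 0.05 is significant, with 336 and 2352 participants

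| x | people out of 336 | relative risk | rejection |
|---|---|---|---|
| 0 | 0 | 1.00 | 5% |
| 0.3% | 1.0 | 1.10 | 7% |
| 0.5% | 1.7 | 1.17 | 9% |
| 1% | 3.4 | 1.33 | 19% |
| 1.5% | 5.0 | 1.50 | 33% |
| 3% | 10.1 | 2.00 | 76% |

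If relabelling may also fall on people who would have had an event anyway, the exposed risk is 1 − (1 − 0.03)(1 − x). At x = 3% that is 1 − 0.97 × 0.97 = 0.0591, a relative risk of 1.97 with about 74% rejection. The choice of formula hardly matters.

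**4. Price of leaving ABI-only PAD out.** Suppose it makes up a share s of the assumed 3% and the relative risk stays at 2. Both risks shrink by (1 − s), so the required number grows by 1/(1 − s). The share s is again an assumption.

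- s = 10%: 336.4/0.9 = 373.8, so 374 exposed (about 2990 in total)
- s = 20%: 336.4/0.8 = 420.5, so 421 exposed (about 3365)
- s = 30%: 336.4/0.7 = 480.5, so 481 exposed (about 3845)

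**5. Why the rule must be the same in both groups.** Suppose ABI-only PAD were dropped among the exposed but still counted among the unexposed. With no true effect the relative risk would be 0.03(1 − s)/0.03 = 1 − s, which is 0.9 to 0.7 for s of 10% to 30%. That is a bias in the opposite direction.

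**The case against.** The strongest reply is that a low ABI by itself produces no event. Follow-up is by telephone and asks about vascular admissions, each case is confirmed from discharge reports, and no repeat ABI is planned. An exposed participant needs an admission and a recorded PAD diagnosis before the criterion comes into play. This stands. A reader might infer that the ABI objective must come out positive by construction; the ascertainment route does not support that.

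Second, the magnitude rests on a rate that the documents do not give. A value of 3% would mean artefactual PAD admissions equal to the whole risk assumed for the unexposed, and at the low end a single relabelled person changes little. Some PAD admissions in people with a low ABI will also be true progression, which is a legitimate outcome. This stands too, and it is why the table is a range and not an estimate.

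Third, baseline ABI is taken with the Vasera device, whereas the event criterion names Doppler. That changes the technique but neither the construct nor the threshold, so it does not answer the point.

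Three extensions are tempting but not supported. The article's silence on masking the adjudicators, and on handling a positive claudication questionnaire at baseline, is detail that a condensed article may leave out. CAVI and pulse wave velocity do not define any event, so the overlap does not reach them. PAD diagnosed by arteriography is not the exposure and need not be discarded.

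**Conclusion.** The point holds as a partial incorporation bias confined to one criterion of one event type and to the ABI part of the first objective. It does not depend on anything the article omits: the event rule is stated, it shares its cut-off with the exposure, and no passage keeps the two apart. The direction is upward for ABI.

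The size cannot be read from the documents. Over the assumed range in the working, with no true effect, it runs from negligible (one relabelled person) to the full design effect (about ten). Those figures assume 3% risk from all other events in both groups, the planned 336 and 2352 participants, an unadjusted comparison, and that every relabelled case is an artefact. Because so few cases can matter, and the ABI estimate is the one the study was sized on, the rule should be settled before events are adjudicated.

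**What to change.** For the ABI part of the first objective, make the main analysis one in which a PAD diagnosis resting only on ABI below 0.9 does not count as an event in any participant. Coronary disease, stroke, PAD diagnosed by arteriography, and amputation, ischaemic ulcer or gangrene continue to count. Apply this identically to exposed and unexposed participants. Report the full event definition as a secondary analysis for ABI, and keep it unchanged for the other markers.

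The change needs wording and, at adjudication, a note of which criterion supported each PAD diagnosis. Its price is fewer events in the ABI analysis. The stated 80% power should be restated for the narrower definition, with the assumed share of ABI-only PAD declared. At an assumed 10% to 30% of the 3% rate, the protocol's formula asks for about 374 to 481 exposed participants in place of 336.

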### Statistical analysis

Percentages will be used to describe categorical variables. Continuous variables will be described with the mean and standard deviation or with the median and the interquartile range as appropriate. Homogeneity among centers will be proved by a Chi-square test or Kruskal-Wallis test depending on the probability distribution of variables. A multivariate analysis by Cox proportional risk models will be performed to examine the contribution of the studied risk factors adjusted by traditional risk factors (age, sex, total cholesterol and HDL cholesterol, smoking status, diabetes and blood pressure).

### Limitations and biases of the study

One of the major difficulties of the study is to achieve a good participation rate. The research team has experience in cohort studies with good success rates (above 70%). Some of the measurements which must be performed are laborious and require a previous training of people who will perform it to ensure accurate, comparable and quality results. This will be fixed by the previous training and a pilot test of 100 participants.

### Ethical considerations

The study has received ethical approval from the Research Ethics Committee of the Institut d'Investigació en Atenció Primària Jordi Gol (Primary Care Research Institute Jordi Gol). Participants will be informed about the examinations performed, they will receive an information document and they will be asked for the informed consent prior to their inclusion. The principles of human experimentation, as the Helsinki Agreement, will be respected. Access to the information obtained from any analysis will be guaranteed. Confidentiality rules will be respected and the participants will be informed about the 5^th ^Article of the15/1999 Spanish organic Law, about the regulation of the automatic processing of personal data (personal data may be automatically processed and the participants have the rights to consult, modify or delete their personal data file).

